## Abstract

**Background::**

Driving pressure has been suggested to be the main driver of ventilator-induced lung injury and mortality in observational studies of acute respiratory distress syndrome. Whether a driving pressure-limiting strategy can improve clinical outcomes is unclear.

**Objective::**

To describe the protocol and statistical analysis plan that will be used to test whether a driving pressure-limiting strategy including positive end-expiratory pressure titration according to the best respiratory compliance and reduction in tidal volume is superior to a standard strategy involving the use of the ARDSNet low-positive end-expiratory pressure table in terms of increasing the number of ventilator-free days in patients with acute respiratory distress syndrome due to community-acquired pneumonia.

**Methods::**

The ventilator STrAtegy for coMmunIty acquired pNeumoniA (STAMINA) study is a randomized, multicenter, open-label trial that compares a driving pressure-limiting strategy to the ARDSnet low-positive end-expiratory pressure table in patients with moderate-to-severe acute respiratory distress syndrome due to community-acquired pneumonia admitted to intensive care units. We expect to recruit 500 patients from 20 Brazilian and 2 Colombian intensive care units. They will be randomized to a driving pressure-limiting strategy group or to a standard strategy using the ARDSNet low-positive end-expiratory pressure table. In the driving pressure-limiting strategy group, positive end-expiratory pressure will be titrated according to the best respiratory system compliance.

**Outcomes::**

The primary outcome is the number of ventilator-free days within 28 days. The secondary outcomes are in-hospital and intensive care unit mortality and the need for rescue therapies such as extracorporeal life support, recruitment maneuvers and inhaled nitric oxide.

**Conclusion::**

STAMINA is designed to provide evidence on whether a driving pressure-limiting strategy is superior to the ARDSNet low-positive end-expiratory pressure table strategy for increasing the number of ventilator-free days within 28 days in patients with moderate-to-severe acute respiratory distress syndrome. Here, we describe the rationale, design and status of the trial.

## INTRODUCTION

Despite recent advances in the care and management of ventilated patients, mortality due to acute respiratory distress syndrome (ARDS) remains high.^(1)^ The severity of ARDS of respiratory etiology was especially evident during the coronavirus disease 2019 (COVID-19) pandemic, during which the mortality of ventilated patients exceeded 50%.^(2^^,^^3)^ Strategies that improve the care of these patients are necessary to decrease morbidity and mortality.

Cyclic stretch of the pulmonary parenchyma is a major contributor to ventilation-induced lung injury (VILI) and varies according to the reduced resting volume of aerated lung in ARDS patients,^(4)^ which in turn is strongly correlated with compliance of the respiratory system. Driving pressure (DP) is an easily measured variable that is equal to the tidal volume divided by the compliance of the respiratory system. Because of these properties, DP has been proposed to be a key mediator of VILI.^(5)^ The association between DP and mortality during mechanical ventilation is supported by observational data.^(4^^,^^6)^ Nevertheless, it is currently unknown whether a treatment strategy limiting DP would be superior to a conventional ventilation strategy in terms of clinical outcomes.^(7)^ Effective strategies to reduce DP include best positive end-expiratory pressure (PEEP) titration and lower tidal volume. The standard PEEP handling strategy involves the arbitrary use of PEEP according to the need for an inspired fraction of oxygen (FiO_2_; "PEEP table").^(8^^,^^9)^ Nonetheless, it can be based on the best respiratory system compliance, which is inversely correlated with DP.^(5)^ By gradually adjusting PEEP levels while monitoring for changes in compliance, clinicians can determine the optimal PEEP setting that minimizes DP.^(10^^,^^11)^ Additionally, reducing the tidal volume below the standard 6mL/kg can further decrease the DP. Implementing these measures in ARDS patients allows for a personalized approach to ventilator management, reducing DP and potentially mitigating VILI.

The objective of this study was to assess whether a mechanical ventilation strategy focused on reducing DP can lead to improved clinical outcomes compared to the ARDSNet low-PEEP table strategy in patients with moderate-to-severe acute respiratory distress syndrome secondary to community-acquired pneumonia (CAP). Community-acquired pneumonia is responsible for 50% of ARDS cases in some clinical trials.^(1^^,^^12)^ Including only CAP patients can improve the recruitment rate, especially during pandemics, and decrease the chance of finding heterogeneous treatment effects between ARDS etiologies.

This study is being conducted to evaluate the impact of this novel approach on key clinical outcomes, such as ventilator-free days and overall improvement in respiratory parameters. By comparing these outcomes between the two ventilation strategies, we aim to determine whether a DP-limiting approach can provide superior benefits regarding clinically important outcomes and potentially pave the way for optimized ventilatory management in ARDS patients.

## METHODS

### Study design

The STAMINA (ventilator STrAtegy for coMmunIty acquired pNeumoniA) study is a randomized, multicenter, open-label trial that will compare two ventilatory strategies: a DP limiting strategy versus a standard strategy (ARDSNet low PEEP table) in patients with moderate-to-severe ARDS secondary to community-acquired pneumonia (CAP) who are hospitalized in intensive care units (ICUs). Eligible patients will receive one of these strategies. The protocol of this study is reported according to the recommendations of the SPIRIT 2013 Statement.^(13)^

### Objectives and outcomes

To evaluate whether a DP-limiting strategy for titrating PEEP according to best compliance is superior in terms of increasing the number of ventilator-free days compared to the standard strategy using a low-PEEP table. The primary, secondary, exploratory and safety outcomes are shown in table 1.

**Table 1 t1:** Outcomes

Outcomes	
Primary	Ventilator-free days within 28 days from randomization or until hospital discharge measured as follows:
	D = zero (if the patient dies within 28 days in the hospital or remains on respiratory support with MV ≥ 28 days)
	D = 28 - x (if the patient is released from the hospital in < 28 days, where x represents the number of days with MV during hospitalization)
	The number of days on MV will be counted as every day the patient spent at least 12 hours on MV. If there is an interruption of MV followed by restart within 48 hours (extubation failure), the entire period will be computed as a single period. For tracheostomized patients, the same criterion is valid. One day of ventilation is computed whenever the patient persists more than 12 hours ventilated
Secondary	1. In-hospital mortality within 90 days
	2. ICU mortality within 90 days
	3. Need for rescue therapies (extracorporeal circulation, recruitment maneuver outside the study protocol, inhaled nitric oxide) within 28 days
Exploratory	1. Oxygenation, measured by the PaO_2_/FiO_2_ ratio during the first 3 days
	2. Driving pressure during the first 3 days
	3. Ventilatory ratio, defined as PaCO_2_ multiplied by minute ventilation divided by 100 × predicted body weight in kilograms × 37.5, measured in the first 3 days
	4. Oxygenation index, defined by MAP × FiO_2_ × 100 ÷ PaO_2_, measured in the first 3 days
	5. Mechanical power, defined by energy transfer (0.098) x respiratory rate x tidal volume x [peak airway pressure – 0.5 x (plateau pressure – PEEP)], measured in the first 3 days
	6. ICU-free days in 28 days
	7. ICU length of stay
	8. Hospital length of stay
Safety outcomes	1. Occurrence of barotrauma (subcutaneous emphysema, pneumothorax, or pneumomediastinum)
	2. Other serious adverse events possibly related to MV within 28 days

MV - mechanical ventilation; ICU - intensive care unit; PaO_2_ - partial pressure of arterial oxygen; FiO_2_ - fraction of inspired oxygen; PaCO_2_ - partial pressure of arterial carbon dioxide; MAP - mean airway pressure; PEEP - positive end-expiration pressure.

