### Sample size

We plan to randomize 500 patients. This number of patients provides a power of at least 90% for detecting a difference of approximately 3 mechanical ventilation-free days and a 5% lower mortality rate in the treatment group.

Considering the raw data from the non-death-related part of the composite outcome (ventilator-free days) and a mortality rate of 60% in the Control group of the CoDEX study^(3)^ as a reference, our simulations reached an average of 4.7 mechanical ventilation-free days in 28 days for the Control group, with quartiles [3.7 - 5.8], standard deviation of 8.2, and a mean of 7.8 mechanical ventilation-free days for the Treatment group, with quartiles [6.5 - 9.2] and a standard deviation of 10.5.

Power estimates were obtained from 2,000 simulations of different scenarios for the primary outcome, considering that death within 28 days would imply zero ventilator-free days, even if the patient was ventilator-free for at least one day during hospitalization. Figure 3 shows the cumulative distribution for the primary outcome from a simulation considering the null model (the effect in the Treatment group was identical to that in the Control group).

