### Data collection time sequence

The data that will be collected are specified in table 5 according to figure 4.

**Table 5 t5:** Data collection schedule

	D-1	D0	D1	D2	D3	D28	ICU discharge	Hospital discharge
Eligibility criteria	X							
Randomization		X						
Informed Consent	X							
Time between ICU admission and randomization		X						
Time of MV before randomization		X						
Date of birth		X						
Ventilatory parameters		X	X	X	X			
Arterial blood gas		X	X	X	X			
Sex at birth	X							
Height	X							
Comorbidities	X							
Pneumonia etiology	X							
Vasopressor dose		X	X	X	X	X	X	
RASS at randomization		X						
SAPS 3 parameters		X						
Protocol support: interventions		X	X	X	X			
Prone position		X	X	X	X		X	
Rescue therapies		X	X	X	X		X	
Vasopressors use		X	X	X	X		X	
Creatinine	X	X	X	X	X			
Total bilirubin	X	X	X	X	X			
Date and time of extubation			X	X	X	X	X	
Data and time of reintubation			X	X	X	X	X	
Vital status at ICU discharge						X	X	
Date of death						X	X	X
Number of days in use of MV in hospital						X	X	X
Date of tracheostomy						X	X	X
Data of ICU discharge							X	
Data of hospital discharge								X
Vital status on hospital discharge								X

ICU - intensive care unit; MV - mechanical ventilation; RASS - Richmond Agitation-Sedation Scale; SAPS 3 - Simplified Acute Physiology Score 3.

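### Table 1 gives no primary-outcome score to survivors who are off the ventilator but still in hospital on day 28, and its ventilator-day count does not start at randomization

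*Protocol article*

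**What the plan says.** In the protocol article, Objectives and outcomes, Table 1 introduces the primary outcome as "Ventilator-free days within 28 days from randomization or until hospital discharge measured as follows". Two scoring rules follow.

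- Zero: "D = zero (if the patient dies within 28 days in the hospital or remains on respiratory support with MV ≥ 28 days".
- Otherwise: "D = 28 - x (if the patient is released from the hospital in < 28 days". The amount to be subtracted is then defined in the same line of the table: "where x represents the number of days with MV during hospitalization".

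A note adds how a ventilated day is recognised: "The number of days on MV will be counted as every day the patient spent at least 12 hours on MV". It sets no start or end date for the count.

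The data collection schedule (Table 5) lists "Number of days in use of MV in hospital" at day 28, ICU discharge and hospital discharge. It also lists "Time of MV before randomization" as a separate item at day 0. The Sample size section restates only the treatment of deaths, "considering that death within 28 days would imply zero ventilator-free days", and says nothing about discharge.

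**The concern.** The two rules do not cover every patient. The second depends on discharge before day 28, so a patient extubated on day 12 who is still on a ward on day 28 satisfies neither. The second rule also uses a different clock from its heading: the window runs from randomization, while x is counted over the hospital stay.

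This is the primary endpoint of an open-label trial whose outcome assessors are not masked (Blinding), with 207 patients already randomized when the article was written (Current trial status). Applied literally, the rule leaves survivors out according to discharge, which is a post-randomization event that the ventilation strategy could affect. If it is not applied literally, someone must decide later how to score these patients.

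**Working it through.** **The plan's own figure.** The Sample size section claims at least 90% power with 500 patients, means of 4.7 and 7.8 days and SDs of 8.2 and 10.5. I assume 250 per arm and a two-sided 5% test; the article states neither.

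- Pooled SD = √((8.2² + 10.5²)/2) = 9.42.
- Normal-approximation power is 95.7% for 7.8 − 4.7 = 3.1 days and 94.5% for 3.0 days, in line with the claim.
- A rank-test simulation with assumed shapes for the survivors' scores gave 78% to 87%, depending on the shape.

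Neither check uses the planned ordinal model, and neither bears on the scoring rule. No point about power is made here.

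**Applying Table 1 literally.** All example patients are alive on day 28. Discharge days are timed from randomization, which Table 1 does not itself specify.

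| Ventilated days | Discharged | Table 1 as written | 28 minus ventilated days from randomization to day 28 |
|---|---|---|---|
| 10 after randomization | day 20 | 18 | 18 |
| 10 after | day 28 | no score | 18 |
| 10 after | day 35 | no score | 18 |
| 27 after | day 40 | no score | 1 |
| 28 after | day 40 | 0 | 0 |
| 2 before + 10 after | day 20 | 28 − 12 = 16 | 18 |

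The first three patients had the same time on the ventilator; only the discharge date decides whether they are scored.

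**How many patients.** The article gives no length-of-stay figure, so the share is an assumption. Inputs from Sample size are control mortality of 60% and a treatment rate 5% lower, read as 55%. I take both as day-28 rates, which the article does not say.

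- Expected survivors: 250 × 0.40 + 250 × 0.45 = 100 + 112.5 = 212.5, about 212.
- If 10% are off the ventilator and in hospital on day 28: 0.10 × 212.5 ≈ 21.
- If 40% are: 0.40 × 212.5 = 85.
- As a share of 500: about 4% to 17%.

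**What zero-scoring them would do.** Let g be that share and v their true ventilator-free days, assumed to be 5 to 10. The arm mean falls by (survival) × g × v.

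- g = 0.10, v = 5: control 0.40 × 0.10 × 5 = 0.20; treatment 0.45 × 0.10 × 5 = 0.225.
- g = 0.40, v = 10: control 0.40 × 0.40 × 10 = 1.60; treatment 0.45 × 0.40 × 10 = 1.80.

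Arm means would fall by about 0.2 to 1.8 days, against a target difference of about 3. With g and v equal in both arms, the difference itself moves by only 0.025 to 0.20 days. It moves more if the strategies differ in time to discharge.

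**Ventilation before randomization.** Under the literal rule, each such day takes one day off every score of the form 28 − x. The 36-hour limit in Table 2 runs from meeting the inclusion criteria, not from intubation, so it does not cap earlier ventilation. As a baseline quantity, though, it is balanced between arms in expectation.

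**The case against.** The best reply is that the meaning can be recovered. The heading, the abstract and the Sample size section all describe a 28-day count with no discharge condition, and a full SAP exists that is not shown here. Nothing says that the unscored patients will be dropped or set to zero, so those consequences are conditional. All of this is fair. It does not close the gap, because the article does not leave the definition to the SAP. It prints an explicit formula, and that formula is incomplete.

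On the clock, the reply is that the lines under the heading are subordinate to it, so x may be meant to start at randomization. That is a reasonable reading, but the definition of x does not say so.

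A reader might infer several stronger things that the documents do not support.

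- **That the outcome cannot be computed.** The rule is deficient, not the data; Table 5 schedules what is needed.
- **That x takes in ventilation after day 28.** If discharge is timed from randomization, the 28 − x rule covers only patients already gone by then.
- **That counting earlier ventilation biases the comparison.** It lowers scores and adds noise, but favours neither arm in expectation.
- **That the planning mean shows how many patients are unscored.** If the 60% is day-28 mortality, 4.7/0.40 = 11.75 free days per control survivor, or 28 − 11.75 = 16.25 ventilated days. That does not give the date of discharge. Inpatients still ventilated through day 28 score zero and do not belong in the gap.
- **That Table 1 and the Sample size section contradict each other on deaths.** The simulation's sentence goes on to speak of the hospital stay, so it may also mean in-hospital deaths.

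**Conclusion.** The point stands in two parts of unequal weight. The main one is certain from the text: Table 1 assigns no primary-outcome score to survivors off the ventilator but in hospital on day 28, or discharged on that day, and no other section supplies one. The lesser one is a conflict between the definition of x, read literally, and the heading's clock; it costs one day of score per ventilated day before randomization.

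The size of the gap is not in the documents. The range of about 21 to 85 of 500 rests on the assumed 10% to 40% of survivors, equal allocation and the planning mortality rates taken at day 28. Because this is the primary endpoint and the missing score depends on a post-randomization event, it should be settled before analysis.

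**What to change.** Replace the two lines in Table 1 with one rule that covers everyone:

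- D = 0 for in-hospital death by day 28 or ventilation through day 28.
- For every other patient, discharged or still in hospital on day 28, D = 28 minus the ventilated days between randomization and day 28. Ventilation before randomization is not counted.

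Use the same rule in the SAP, and confirm that the power simulation uses it.

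As a matter of consistent wording, state in both Table 1 and Sample size whether death after discharge but before day 28 scores zero.

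The cost is wording in the protocol and SAP, plus a check of the simulation code. The extubation, reintubation, discharge and death dates and the pre-randomization ventilation time in Table 5 are sufficient. One caution: Table 5 has a day-28 column for date of death, but the article does not say that discharged patients are contacted then. If the sponsor chose to score post-discharge deaths as zero, it would first need to confirm how vital status is obtained.

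### Table 1 gives 28 − x to patients who die after discharge, or who are released on the ventilator, before day 28, and its death rule differs from the one used for the sample size

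*Protocol article*

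**What the plan says.** The primary outcome is defined in Table 1 (Objectives and outcomes) as "Ventilator-free days within 28 days from randomization or until hospital discharge". Two scores follow.

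- The lowest score, zero, applies under this condition: "if the patient dies within 28 days in the hospital or remains on respiratory support with MV ≥ 28 days".
- The other score subtracts x from 28 and applies in a different case: "if the patient is released from the hospital in < 28 days, where x represents the number of days with MV during hospitalization".

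The Sample size section states the death rule used in the power simulations: "death within 28 days would imply zero ventilator-free days, even if the patient was ventilator-free for at least one day during hospitalization". It sets no explicit limit on where the death occurs.

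In Table 5 (Data collection time sequence) the MV item is "Number of days in use of MV in hospital". Date of death and the dates of extubation and reintubation each have a D28 entry. No item records whether the patient was on MV when leaving the hospital.

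**The concern.** Table 1 confines observation to the hospital stay in three places: the window, the death clause and the count x. The score nevertheless credits every day from release to day 28 as ventilator-free. For a patient discharged alive and breathing unaided, that is a reasonable convention. For a patient who dies soon after discharge, or who leaves on MV, the credited days were not lived or not ventilator-free.

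The outcome is ranked in an ordinal model, so such a patient moves from the bottom category to somewhere among the survivors, and can pass the average survivor. Staff who decide on release know the allocation, so the misplacement need not balance between arms. The outcome assumed in the power simulations and the outcome defined for analysis also differ for post-discharge deaths.

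**Working it through.** **1. The plan's own figure.** The Sample size section claims "power of at least 90% for detecting a difference of approximately 3 mechanical ventilation-free days" with 500 patients. Inputs: means 4.7 and 7.8, SDs 8.2 and 10.5. Assumptions: 1:1 allocation (250 per arm) and two-sided 0.05.

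- Difference: 7.8 − 4.7 = 3.1 days.
- Pooled SD: √[(8.2² + 10.5²)/2] = 9.42.
- Normal-approximation power: 0.957 for 3.1 days and 0.945 for 3.0 days.

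On this basis the stated figure is reproduced. The point below does not depend on it.

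**2. The two death rules side by side.** Take a patient with 7 MV days, discharged and then dead before day 28.

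- Table 1: the death was not in hospital and MV was under 28 days, so D = 28 − 7 = 21.
- Sample size section: death within 28 days, so D = 0.

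**3. Release on MV.** Assume MV on every day from randomization to release on day d, so x = d and the release rule gives 28 − d.

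| Day of release on MV | 3 | 5 | 7 | 10 | 14 | 20 |
|---|---|---|---|---|---|---|
| 28 − x | 25 | 23 | 21 | 18 | 14 | 8 |

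If the patient is still ventilated at day 28, the MV clause of the zero rule can also be read to apply. That gives 0, and Table 1 does not say which rule prevails.

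For scale, the implied mean among survivors is 4.7/0.40 = 11.8 days in control (60% mortality). In the treatment arm it is 7.8/0.45 = 17.3 days, reading the 5% lower mortality as percentage points. A ventilated release by about day 10 (18 or more) outranks the average survivor in either arm. A release on day 20 (8) does not.

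**4. Effect on an arm mean.** Shift = (share of arm mis-scored) × (score given − correct score). The share is assumed, because the documents give none. A gap of 19 is the middle of scores from 14 to 24, and 22 corresponds to release on day 6; both take the correct score as 0.

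- 1% of an arm: 0.01 × 19 = 0.19 to 0.01 × 22 = 0.22 days. Divided by 3.1, this is 6% to 7%.
- 2%: 0.38 to 0.44 days (12% to 14%).
- 5%: 0.95 to 1.10 days (31% to 35%).

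**5. Effect on the comparison.** The simulation used 250 per arm, a rank test and 2,000 runs. Scores were drawn from an assumed zero-inflated beta-binomial matched to the stated means and SDs and to 60%/55% mortality. Affected patients have a true score of 0 but are scored 14 to 24.

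| Affected, control / treatment | Mean difference (days) | Rejection rate |
|---|---|---|
| Planned effect, 0% / 0% | 3.10 | 0.80 |
| Planned effect, equal rates of 1% to 10% | about 3.1 | 0.80–0.83 |
| Planned effect, 2% / 0% | 2.75 | 0.67 |
| Planned effect, 5% / 0% | 2.15 | 0.40 |
| No effect, 0% / 0% | 0.00 | 0.05 |
| No effect, 5% / 5% | 0.02 | 0.07 |
| No effect, 2% / 5% | 0.58 | 0.13 |
| No effect, 0% / 5% | 0.96 | 0.24 |

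The small excess in the 5%/5% row arises because the number re-scored is drawn independently of the number of zeros, which adds variance. It is not a bias, since the mean difference stays near zero. Equal rates do little harm; unequal rates do.

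**The case against.** The case against has several good parts.

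- **Transfer.** A reader might infer that patients transferred on MV, for example for extracorporeal support, are systematically given near-best scores. The article does not say that release includes transfer. Extracorporeal support appears only as a rescue therapy, and transfers may be handled in the SAP, which is not shown. Near-best also fits only early exits.
- **The zero rule may already catch some patients.** Its MV clause has no in-hospital limit, so a patient sent home on MV and still ventilated at day 28 may score 0. This makes the text ambiguous for that patient rather than plainly wrong. It does not cover a post-discharge death or someone liberated between release and day 28.
- **Data capture.** It would be wrong to say that nothing is scheduled at day 28. Table 5 has date of death and extubation and reintubation dates there. But even a recorded post-discharge death would not score zero under Table 1.
- **Bias.** A reader might infer that the comparison is biased. No exit rate is given and no difference by arm is shown. The true score is also not always 0: a patient released on MV on day 6 and liberated on day 12 would have about 16.
- **Power.** The 0.80 baseline in the simulation does not show that the stated 90% is wrong. It rests on an assumed distribution, and the shape used by the trial is not shown.
- **The sample-size sentence** mentions hospitalization and might have had only in-hospital deaths in mind. That is a further reason to align the two texts.
- **In-hospital mortality.** A reader might see the same flaw in this secondary outcome. Ending at discharge is simply its definition.

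What stands is the literal scoring of post-discharge deaths, the credit for days after release on MV, the missing precedence, and the disagreement with the Sample size section.

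**Conclusion.** The concern holds in limited form. Followed literally, Table 1 scores a patient who dies after discharge but before day 28 as 28 − x (21 in the worked case), against zero in the Sample size section. It also credits days after release on MV, or leaves two rules competing. This is in the stated definition of the primary outcome and is not a detail left to another document.

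The size is unknown because exit rates are not given. Each 1% of an arm affected shifts that arm's mean by about 0.2 days (6–7% of 3.1), assuming a correct score of 0 and a gap of 19 to 22 days. Bias in the treatment comparison requires rates that differ by arm. Open-label care makes that possible, and the documents do not show that it happens. The claimed power and the sample size are not called into question.

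**What to change.** In Table 1:

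- Give D = 0 for death by day 28 in any location. This matches the Sample size section and uses the date of death already scheduled at D28.
- For patients released before day 28, apply 28 − x only to those who leave alive and off MV.
- Count a patient released or transferred on MV as ventilated from that date to day 28 unless liberation is documented, and state that this rule takes precedence over 28 − x.

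In Table 5, add one item: MV status at hospital release. Align Table 1, the Sample size section and Table 5. In-hospital mortality needs no change.

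The cost is new wording and one data item. The sample size stays as it is, since the simulations already score death within 28 days as zero. The downside is that some patients liberated elsewhere without documentation will be scored too low. For the 207 patients randomized when the article was written, status after release may be incomplete, so add a sensitivity analysis under the present Table 1 scoring.
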